### 3.0 Describe and justify the exclusion criteria for participants:

(1) Patients with curves  $>45^\circ$  may be surgical candidates, and will be excluded.

-Our clinic and the Scoliosis research foundation clearly recommend that patients with such large curves should be considered for surgery. In practice, these patients may be prescribed surgery and not deemed candidate for an exercise program.

(2) Patients who have had surgery will be excluded.  
 -Previous surgical intervention could have a confounding effect in the efficacy analysis.

-A separate study could examine the effect of exercises combined with surgical correction but the current study will not address this question.

(3) Patients under the age of 10 will not be included, as the Schroth exercise program is not designed for juveniles. The level of comprehension may be too difficult for ages 5-10 (age of diagnosis with JIS). Patients over the age of 16 are excluded as treatment and observation at the Edmonton Scoliosis clinic is complete at age 18 and patients over 16 years old are likely to have reached skeletal maturity and in that group exercises prescription would be optional and target a different goal than simply stopping curve progression.

4) Patients with Risser signs in excess of 3 are deemed skeletally too mature to use exercises to slow progression. The exercises may be used in such a group but the goal would be different and does not correspond to the rationale that may convince surgeons managing scoliosis in North America to prescribe intensive exercise programs in patients with scoliosis.

### 4.0 Participants

**4.1 How many participants do you hope to recruit (including controls, if applicable?)**

100

**4.2 Of these, how many are controls, if applicable?**

26

**4.3 If this is a multi-site study, how many participants do you**

**anticipate will be enrolled in the entire study?**

208

## 5.0 Justification for sample size:

Primary and secondary aim 1: A sample of 129 subjects per group will be sufficient to detect a 0.31 effect size when comparing the change in outcomes between the exercise and control groups with 80% power using a unilateral test and an alpha of 0.05 (104 Schroth and 104 controls in this study + 25 Schroth and 25 controls in the pilot allows a total of 129 per group). We anticipate >80% completion rate based on published data and because the pilot dropout rate was <10%. Our per-protocol sample may drop slightly however, we are planning intent to treat analyses where we will carry-forward the last known observation from our participants.

A unilateral hypothesis is justified, for this superiority trial, by positive published data and our pilot data. The pilot effect size for the Cobb angle was 0.32 and many secondary outcomes had effect sizes exceeding what we are powered to detect as significant. A trial conclusive in favour of exercises would have a significant impact in America. A trial failing to demonstrate positive results would have less impact as Schroth exercises are not currently prescribed. We believe that a 0.32 effect size is clinically important, feasible, and would justify implementing a Schroth program. The trial duration is relatively short which justifies aiming to detect a small effect size (0.2-0.5) .

It would be inadequate to power the trial to detect too small an effect size as patients and families will likely demand evidence of clinically important effects before committing efforts and time required of Schroth exercise programs. For the secondary aim comparing the results of subjects in the control group who first complete 6 months as controls to their results after completing 6 months of Schroth exercises, an effect size of 0.27 (n=106) could be detected as significant with a power of 0.80, an alpha of 0.05 with a unilateral test.

ID: Pro00043397

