### **Methods**

#### Subjects

Female patients with AIS, JIS, or syringomyelia without chiari (n=208) will be recruited in Edmonton, Calgary and Montréal. Inclusion criteria are: (1) curves 10°-45°, (2) age 10-16 (3) All Schroth curve types (3c, 3cp, 4c and 4cp), (4) treated with or without brace (5) living within 1 hour of the study site and (6) with Risser sign less than or equal to 3. Those planning or post-surgery will be excluded.

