## **Analyses:**

Intention to treat (by carrying forward last known value) linear mixedmodel analyses will be used to assess differences in group changes from baseline, to 3 and 6-month while adjusting for covariates. Separate analyses will be conducted for each outcome. To screen for variables associated with each of the outcomes variables, we will use univariate linear mixed models and include all relevant covariates (age, time since menarche, apex levels, physical activity, self-efficacy, and bracing compliance may have associations with risk of progression). Multiple linear mixed models will be tested including covariables found significant at  $P=0.20$  in the univariate analysis, and after screening for multicollinearity. Results will be presented as effect sizes with confidence intervals and one-sided P-values. Statistical analyses will be performed using SAS version 9.1.

For subjects initially in the control group later completing 6 months of exercises, intention to treat linear mixed-model analyses will be used to assess differences between the two periods (standard care vs standard care + Schroth) in changes from baseline, to 3 and 6-month, while adjusting for covariates. Screening for covariates will be done as described above. In this model, treatment period is a dependent factor.

To determine if exercises effects are maintained at 12 months and discharge exams, linear mixed- model analyses will also be used to quantify the effect sizes corresponding to changes from 6 to 12 months and to discharge by combining data from all patients after participating in the exercise program.

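### The stated 80% power holds only if 50 patients from an already known pilot are pooled in; the 208 newly randomised patients alone give 72%, and pooling does not keep a 5% error rate once the pilot result is known

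*Protocol*

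**What the plan says.** Protocol section 4.2, item 5.0 (Justification for sample size), states: "A sample of 129 subjects per group will be sufficient to detect a 0.31 effect size", "with 80% power using a unilateral test and an alpha of 0.05". The 129 is then explained: "104 Schroth and 104 controls in this study + 25 Schroth and 25 controls in the pilot allows a total of 129 per group".

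The same item reports what the pilot found: "The pilot effect size for the Cobb angle was 0.32". It uses the pilot in two further ways:
- for the direction of the test: "A unilateral hypothesis is justified, for this superiority trial, by positive published data and our pilot data";
- for the effect worth finding: "We believe that a 0.32 effect size is clinically important, feasible, and would justify implementing a Schroth program".

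The size of this study is given under Subjects in section 2.1: "Female patients with AIS, JIS, or syringomyelia without chiari (n=208) will be recruited in Edmonton, Calgary and Montréal". Section 4.2 also gives 208 for the entire multi-site study. The item on closely linked research describes the pilot as a study with its own ethics approval, which the present one extends to several sites.

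The Analyses part of section 2.1 plans linear mixed models, with last values carried forward and one-sided P-values. On scope it says only "Separate analyses will be conducted for each outcome". It does not say whether pilot patients enter the between-group comparison.

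**The concern.** The power statement describes 258 patients, but the trial randomises 208. The other 50 come from a completed study whose result was on the table when the design was written. Their evidence is used once as part of the case for a one-sided test, and would be used again as data in that test.

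Each possible analysis set therefore has its own problem. If the primary analysis uses the 208, the power is lower than stated. If it uses the 258, part of the test statistic is already fixed at a favourable value, and the nominal 5% no longer describes the risk of a wrong conclusion from the data still to be collected. The protocol presents the trial as confirmation of earlier, weaker evidence and expects it to inform whether clinics adopt the programme. A reader would take 80% power and 5% alpha as properties of the new trial.

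**Working it through.** **Inputs** (all from section 4.2, item 5.0): effect 0.31; one-sided alpha 0.05; 104 new and 25 pilot patients per group; pilot Cobb effect 0.32.

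**Assumptions** (not stated in the protocol): 0.32 is a standardised mean difference in favour of exercise, based on 25 evaluable patients per arm, and pooling is simple, with no study term. The evaluable number is varied below.

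**1. The plan's own figure.** Power ≈ Φ(d·√(n/2) − 1.645).
- n = 129: 0.31 × √64.5 = 2.490; 2.490 − 1.645 = 0.845; power 80.1% (79.9% by noncentral t).
- The figure reproduces, so 80% is the power of the pooled 258.

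**2. The new patients alone.**
- n = 104: 0.31 × √52 = 2.235; 2.235 − 1.645 = 0.590; power 72.3% (72.0% by noncentral t).
- At 0.32, the effect that the protocol calls clinically important: 74.6%.
- Detectable effect at 80% power: (1.645 + 0.842) × √(2/104) = 0.345 (0.346 by noncentral t).
- Reaching 80% at 0.31 without the pilot needs 129 new patients per group, or 258 in all.

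**3. The pooled test, given the pilot result.**
- Pilot z = 0.32 × √(25/2) = 1.131, one-sided P about 0.13. The pilot is favourable but not significant.
- Pooled Z = √(25/129) × 1.131 + √(104/129) × Z_new = 0.498 + 0.898 × Z_new.
- Rejection needs pooled Z > 1.645, so Z_new > (1.645 − 0.498)/0.898 = 1.277.
- With no effect in the new patients, P(Z_new > 1.277) = 10.1% (simulation 10.05%).
- On the effect scale, the new patients need an observed 1.277/√52 = 0.177 to reach significance after pooling, against 1.645/√52 = 0.228 on their own.
- With a true effect of 0.31 in the new patients, the same formula gives Φ(2.235 − 1.277) = 83%. Given this pilot, pooling raises the chance of success from 72% to 83% when the effect is real, and from 5% to 10% when it is absent.

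**4. How the error rate moves with the assumptions.**

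| What is conditioned on | Rejection of a true null in the new patients |
|---|---|
| Pilot effect 0.32, 25 evaluable per arm | 10.1% |
| Pilot effect 0.32, 23 per arm | 9.6% |
| Pilot effect 0.32, 20 per arm | 8.8% |
| Only that the pilot was favourable | 8.4% |
| Nothing: direction and pooling fixed before the pilot | 5% |

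**The case against.** The strongest reply is that pooling is openly disclosed, that this study is an extension of the pilot, and that a pooled one-sided test keeps 5% when averaged over all pilot results. The disclosure is real. The 5% requires direction and pooling to have been fixed before the pilot was seen, whereas item 5.0 itself cites the pilot data as a reason for the direction. Conditioning only on a favourable pilot already gives 8.4%.

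Several stronger readings are tempting, but the documents do not support them:
- **A flat false-positive rate of 10%.** This is a conditional probability. It depends on how many patients the 0.32 was based on and how the effect size was defined, and the protocol gives neither.
- **The pilot alone set the direction and the target.** Published data are named beside the pilot as grounds for the direction. The powered value, 0.31, is what 129 per group can detect; it is not the pilot's 0.32. The item also supports aiming at a small effect by the short trial duration.
- **The Analyses text fixes the set at 208 and so contradicts item 5.0.** It is silent on pooling. The lack of a study term there is model detail that a statistical analysis plan may supply.
- **Dropout lowers the power to about 64%.** At 80% to 90% completion, a completers' analysis of the new patients would have about 64% to 68% power. The plan carries last values forward, so its analysis set stays at 104 per group, and item 5.0 expects more than 80% completion.

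Section 4.5 says enrolment is complete, so restating the power cannot change the sample. What can still be settled is which patients carry the confirmatory claim.

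**Conclusion.** The concern holds in this form: 80% power at 0.31 is a property of 258 pooled patients, not of the trial. The 104 per group randomised here have 72% power at 0.31 and 80% power at about 0.35, before any loss of information from dropout. This part uses only the protocol's own figures.

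If the pilot is pooled, the chance of rejecting a true null in the new patients, given what was already known, is about 9-10% rather than 5%. This part rests on a standardised mean difference favouring exercise, 20 to 25 evaluable pilot patients per arm, and simple pooling.

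A statistical analysis plan could choose either set. It could not make 80% power at 0.31 and a 5% error rate both true of the new evidence. The shortfall is about 8 points of power, it can be seen from the disclosed pooling, and it is curable by wording, so this should be fixed but does not invalidate the trial.

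**What to change.** - Name the 208 newly randomised patients as the primary confirmatory analysis set, in item 5.0 and in the Analyses text.
- Restate item 5.0 as: 104 per group gives 80% power for an effect of 0.35 and 72% power for 0.31, one-sided alpha 0.05, before attrition.
- Report the 258-patient pooled estimate as supportive only, from a model with a fixed effect for study (pilot versus main).

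The cost is wording in the protocol and the analysis plan; no further patients are needed. The downside is that the stated power and detectable effect become less favourable.

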**Pro00043397**

Status: Approved

4.3 Recruitment of Participants (Health)

## 4.3 Recruitment of Participants (Health)

## 1.0 Recruitment

**\* 1.1 How you will identify potential participants? Please be specific.** (i.e. Will you be screening clinical lists, accessing electronic health records (e-clinician), asking staff from a particular area to let you know when a patient meets criteria, will you be sitting in the emergency department waiting room, etc?)

At the regular specialized scoliosis clinic at each site, the clinic's nurse will determine the eligibility of each patient and refer a patient to our research coordinator for more information on the study. If a patient decides to participate, an informed consent will be obtained. The contact information of eligible and consented patients will be forwarded to the researchers, who will coordinate with patients from that point on.

Primary care physicians identifying potential candidates will suggest these patients contact the PI to be informed of the study. Interested such participants will be referred to the specialized scoliosis clinic to confirm eligibility and begin participation.

**1.2 If you are using patient/clinical records to identify potential participants for research purposes, will someone from the data custodian/clinical care team seek prior consent of the participant to allow the researcher to look at their records?**

☐ Yes ☐ No

**1.3 Once you have identified a list of potentially eligible participants, indicate how the potential participants' names will be passed on to the researchers AND how will the potential participants be approached about the research.**

**1.4 Outline any other means by which participants could be identified**(e.g. response to advertising such as flyers, posters, ads in newspapers, websites, email, list serves, physical or community organization referrals):

## 2.0 Pre-Existing Relationships

**2.1 Will potential participants be recruited through pre-existing relationships with researchers** (e.g. Will an instructor recruit students from his classes, or a physician recruit patients from her practice? Other examples may be employees, acquaintances, own children or family members, etc)?

☒ Yes ☐ No

**2.2 If YES, identify the relationship between the researchers and participants that could compromise the freedom to decline** (e.g. clinician/patient, professor/student):

Some of the study team members are involved in the management of patients attending the site's specialized Scoliosis Clinics. Patients with scoliosis from the sites' specialized Scoliosis Clinic will be informed of the

study and invited to participate by the clinic coordinator when arranging clinic visits. The clinic coordinator will send the study information by email or by phone when booking the clinic visit. The booking is not dependent of patient's agreement to participate. Once informed, patients will contact the researcher to learn more about the project and arrange participation in the study. The coordinator will explicitly mention that patient may refuse to participate. The surgeon may answer questions about the project during the patient's visit but will not be directly involved in the enrollment process. The clinic's nurse practitioner will assist in determining patient's eligibility but will not decide if a patient is ultimately eligible or not (this will be confirmed during the baseline evaluation).

### **2.3 How will you ensure that there is no undue pressure on the potential participants to agree to the study?**

### **3.0 Will your study involve any of the following (select all that apply)?**

Reimbursement for any expenses incurred by the participants, e.g. parking costs, child care, lost wages, etc

ID: Pro00043397

Pro00043397

4.5 Informed Consent Determination

Status: Approved

## **4.5 Informed Consent Determination**

### **1.0 Describe who will provide informed consent for this study (i.e. the participant, parent of child participant, substitute decision maker, no one will give consent – requesting a waiver)**

#### **1.1 Waiver of Consent Requested**

If you are asking for a waiver of participant consent, please justify the waiver or alteration and explain how the study meets all of the criteria for the waiver. Refer to [Article 3.7 of TCPS2](#) and provide justification for requesting a Waiver of Consent for ALL criteria (a-e)

#### **1.2 Waiver of Consent in Individual Medical Emergency**

If you are asking for a waiver or alteration of participant consent in individual medical emergencies, please justify the waiver or alteration and explain how the study meets ALL of the criteria outlined in [Article 3.8 of TCPS2](#) (a-f).

### **2.0 How will consent be obtained/documented? Select all that apply**

Signed consent form  
Verbal consent

**If you are not using a signed consent form, explain how the study information will be provided to the participant and how consent will be obtained/documented. Provide details for EACH of the options selected above:**

Since we have completed enrollment only participants in need of follow-up will need to have a consent amendment to continue their participation.

Participants will be called prior to appointments and will be advised that the risk involved with this study has changed due to increased possibility for exposure to COVID-19. Participants will be read the telephone script (added in documentation) and will be asked if they would like to continue to be enrolled in this study. Should they agree to continue to participate, we will sign that we have their verbal consent. Participants will be provided with a copy of this verbal consent at their next in person visit.

**3.0 Will every participant have the capacity to give fully informed consent on his/her own behalf?**

☐ Yes ☐ No

**3.1 Explain why participants lack capacity to give informed consent (e.g. age, mental or physical condition, etc.).**

Participant will be considered as unable to give informed consent because all enrolled are expected to be younger than 17 years. Since enrolling in the study will require parental support (driving to treatments for up to 6 months, assent from patients and parental consent are the ideal informed consent strategy for this study.

**3.2 Will participants who lack capacity to give full informed consent be asked to give assent?**

☒ Yes ☐ No

**Provide details. IF applicable, attach a copy of assent form(s) in the Documentation section.**

Assent forms will be provided by email (of fax as needed) prior to the visit and signed during the visit after discussing the study with the coordinator. Opportunities to ask question by phone or before beginning study procedures will be available.

**3.3 In cases where participants (re)gain capacity to give informed consent during the study, how will they be asked to provide consent on their own behalf?**

We do not anticipate that many patients will be followed-up until 18 years old when they would be able to consent on their own. If they do, we will have them complete a consent form once they reach the age of consent. Nevertheless, all subjects will complete an assent form to ensure that they are informed of the nature of what is expected of them in the study.

**4.0 What assistance will be provided to participants or those consenting on their behalf, who may require additional assistance? (e.g. non-English speakers, visually impaired, etc.)**

Researchers will be available to answer question on site when the consent/assent form is signed. Forms will be emailed ahead of participating to ensure the participants have plenty of time to digest the information. The researchers could be contacted via phone or email to answer questions ahead of participation if needed. All subject are under 18yo and will be invited to provide assent and parental consent will be obtained.

**5.0 \* If at any time a PARTICIPANT wishes to withdraw from the study or from certain parts of the study, describe when and how this can be done.**

Participants may do so at any time.

**6.0 Describe the circumstances and limitations of DATA withdrawal from the study, including the last point at which participant DATA can be withdrawn (i.e. 2 weeks after transcription of interview notes)**

Data withdrawal is possible by patient request at anytime before the analyses are completed.

**7.0 Will this study involve any group(s) where non-participants are present? For example, classroom research might involve groups which include participants and non-participants.**

☐ Yes ☒ No

ID: Pro00043397

Pro00043397

Status: Approved

4.6 Expense Reimbursements and Incentives

## 4.6 Expense Reimbursements and Incentives

### 1.0 Expense Reimbursements:

**1.1 Describe in detail the expenses for which participants will be reimbursed, the value of the reimbursements per item as well as the total maximum reimbursement and the reimbursement process (e.g. participants will receive a cash reimbursement for parking at the rate of \$12.00 per visit for up to three visits for a total value of \$36.00)**

Patients will be asked to commit time for the assessments, the treatments (individual and weekly group classes), and the home exercise routine. No funds are available to compensate patients for their time. Evaluations and treatments are provided at no charge to patients or their insurance. Transportation to the evaluations and treatments are the responsibility of the patients/ parents and will not be reimbursed.

Participants will be provided with parking coupons for each visit to our sites.

**1.2 If you will be collecting personal information to reimburse or pay participants, describe the information to be collected and how privacy will be maintained.**

Not applicable.

## **2.0 Incentives:**

**2.1 Will participants receive any incentives for participating in this research (i.e. gift card, cash payment, prize draw)? If yes, provide details of the value, including the likelihood (odds) of winning for prize draws and lotteries.** [The Use of Incentives In Research](#)

Patients will be asked to commit time for the assessments, the treatments (individual and weekly group classes), and the home exercise routine. No funds are available to compensate patients for their time. Evaluations and treatments are provided at no charge to patients or their insurance. Transportation to the evaluations and treatments are the responsibility of the patients/ parents and will not be reimbursed. Participants will be provided with parking coupons for each visit to out sites.

